#### Midtreatment, End-of-Treatment, and 2-Month Follow-Up Assessments

After the baseline visit, participants will complete 3 follow-up assessments: (1) midtreatment assessment (weeks 8-9), (2) end-of-treatment assessment (to be administered within 2 weeks of completing the final lesson or reaching the end of the study period; weeks 16-20), and (3) a 2-month follow-up (2 months after the end of treatment; weeks 24-28). The exact assessment timeline may vary for each participant according to scheduling availability and whether the 16 lessons are completed before the end of the study period.

### Statistical Analysis

#### Feasibility and Acceptability

We will use descriptive statistics to examine feasibility and acceptability of *CBT-based Mindful Courage*. Both groups will be included in analyses of recruitment feasibility, randomization, and assessment completion, whereas only participants in the *CBT-based Mindful Courage* group will be included for evaluating acceptability and feasibility of intervention completion. Specifically, we will compute average scores and frequencies for all feasibility and acceptability benchmarks.

#### Outcomes and Mechanisms

On an exploratory basis, we will evaluate changes in outcomes and mechanisms from baseline to each subsequent assessment point using linear mixed models, separately for participants in each of the conditions (n=20 in each condition). Mixed models enable the inclusion of all participants regardless of missing data (ie, an intent-to-treat analysis). We will also calculate Cohen *d* effect sizes for changes within condition.

## Results

The study was funded in April 2023. Data collection began in November 2025. We anticipate that the recruitment will be completed by November 2026. At the time of initial manuscript submission, no participants had been recruited. We expect results to be analyzed by May 2027 and published by May 2028.

## Discussion

### Anticipated Findings

This protocol describes the design of a pilot RCT with the primary objectives of evaluating the feasibility and acceptability of a digital program combining CBT and mindfulness training for BED—*CBT-based Mindful Courage*. As exploratory objectives, we will evaluate changes in binge eating frequency, global ED symptoms, clinical impairment, and depressive symptoms (as outcomes), as well as emotion dysregulation, dietary overrestriction, and trait mindfulness (as potential mechanisms).

On the basis of our prior research [22,23,32], we anticipate that *CBT-based Mindful Courage* will be acceptable and feasible, setting the stage for an efficacy trial. Our recent study evaluating an 8-week version of *Mindful Courage* for anorexia nervosa and bulimia nervosa concluded that intervention feasibility was excellent and that the intervention was acceptable to participants [23]. Furthermore, our pilot trial evaluating a single-session version of *Mindful Courage* for BED demonstrated excellent acceptability and 100% intervention completion [32]. Preliminary efficacy was demonstrated in both cases, with significant improvements in ED symptoms as well as secondary outcomes (eg, clinical impairment).

### Strengths and Limitations

This study will advance our understanding of the feasibility and acceptability of integrating CBT with mindfulness training for EDs. This trial is also innovative as the first digital intervention for BED to place a major emphasis on mindfulness training. Overall, this study advances our understanding of the viability of digital mindfulness–based treatment as a modality for treating EDs in general, and BED in particular.

This study has several potential limitations. First, a common problem with digital treatments and online research studies is high dropout rates, from both the treatment and study assessments. To overcome this problem, we will implement various retention strategies such as graduated incentives and the inclusion of coaches. Second, we have a relatively low sample size. Nevertheless, the sample size is sufficient to evaluate our primary feasibility and acceptability aims, and this type of test follows the NCCIH model for treatment development [33]. Third, the sample may not be representative of the population.

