## Methods

### Participant Recruitment and Eligibility Criteria

Participants will be recruited throughout the United States using advertisements posted on social media. The target sample size is 40 (n=20 in each treatment arm). This sample size was based on balancing various considerations, including ethical considerations (eg, participants’ time), resource use, prior feasibility trials [35], and availability of funding. Participant eligibility criteria are shown in Textbox 1.

Participant eligibility criteria.

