#### Feasibility Benchmarks

Benchmarks for feasibility are based on previous digital interventions for EDs [31,62-64], and include (1) feasibility of recruitment (40 participants randomized); (2) feasibility of randomization (75% of eligible screens randomized); (3) intervention completion (34/40, 85% of randomized individuals completing at least 1 module; average completion rates of 60% for the 16 lessons) assessed objectively via Qualtrics; (4) completion rates for midtreatment, end-of-treatment, and 2-month follow-up visits (32/40, 80% of participants completing the midtreatment visit, 30/40, 75% of participants completing the end-of-treatment visit, and 26/40, 65% of participants completing the follow-up visit).

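### The claim that N=40 is sufficient for the primary aims has no stated precision basis: the benchmarks screen out gross failure but not shortfalls of 5 to 10 points, and should carry intervals

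*Protocol article*

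**What the plan says.** Four places in the protocol article bear on this point.

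- **Participant Recruitment and Eligibility Criteria.** The target is 40, 20 per arm. The reasons given are practical: "This sample size was based on balancing various considerations, including ethical considerations (eg, participants’ time), resource use, prior feasibility trials [35], and availability of funding".
- **Feasibility Benchmarks and Acceptability Benchmarks.** Each benchmark is a single cut-off. Visit completion is set at 80% (32/40) for midtreatment, 75% for end of treatment ("30/40, 75% of participants completing the end-of-treatment visit") and 65% (26/40) for follow-up. Starting the intervention is set as "34/40, 85% of randomized individuals completing at least 1 module". Mean lesson completion is set at 60% of 16 lessons, and mean acceptability ratings at above 3.5 on a 1–5 scale.
- **Statistical Analysis, Feasibility and Acceptability.** The approach is descriptive: "we will compute average scores and frequencies for all feasibility and acceptability benchmarks". Visit completion uses both arms. Intervention completion and acceptability use the intervention arm only, so about 20 people.
- **Strengths and Limitations.** The article concedes the size ("Second, we have a relatively low sample size") and then states that "the sample size is sufficient to evaluate our primary feasibility and acceptability aims", adding that this type of test follows the funder's treatment-development model.

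**The concern.** Feasibility and acceptability are the primary goals, and the Discussion expects a favourable result to prepare the way for an efficacy trial. The sufficiency sentence is a positive claim about the design, but nothing in the article supports it. The stated grounds for N are not grounds of precision, and comparing a bare proportion with a cut-off does not show how far the true rate may lie from it.

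What is at stake is how much a benchmark reported as met can support. If follow-up comes out at exactly 26/40, the planners of the next trial need to know whether true retention could plausibly be near 50%. The article itself names dropout as its first limitation.

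A second matter affects the denominator. The module-completion benchmark is printed out of 40, while the analysis section restricts intervention completion to the intervention arm. Only that arm has access to the lessons.

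**Working it through.** **Inputs from the article.** N=40, 20 per arm; cut-offs 32/40, 30/40, 26/40 and 85% for module completion. The printed counts are arithmetically right: 32/40 = 80%, 30/40 = 75%, 26/40 = 65%, 34/40 = 85%. On the intervention-arm denominator, 85% of 20 is 17. No alpha, power, precision target or minimum acceptable rate is given, so there is no sample-size calculation to reproduce.

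**Step 1. What a just-met benchmark is compatible with.** Exact (Clopper–Pearson) 95% limits for x out of n are the 2.5% quantile of Beta(x, n−x+1) and the 97.5% quantile of Beta(x+1, n−x).

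| Benchmark just met | Exact 95% CI | Distance below / above (points) |
|---|---|---|
| 32/40 (80%) | 64.4–90.9% | 15.6 / 10.9 |
| 30/40 (75%) | 58.8–87.3% | 16.2 / 12.3 |
| 26/40 (65%) | 48.3–79.4% | 16.7 / 14.4 |
| 17/20 (85%) | 62.1–96.8% | 22.9 / 11.8 |

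**Step 2. Chance of passing when the true rate falls short.** With cut-off r, the pass probability at true rate p is P(X ≥ r), X ~ Binomial(n, p).

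| True rate relative to benchmark | 32/40 | 30/40 | 26/40 | 17/20 |
|---|---|---|---|---|
| 5 points below | 0.30 | 0.31 | 0.32 | 0.41 |
| 10 below | 0.11 | 0.12 | 0.13 | 0.23 |
| 15 below | 0.030 | 0.035 | 0.040 | 0.11 |
| 20 below | 0.006 | 0.007 | 0.009 | 0.044 |

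The bottom row shows that gross failure is caught. The top two rows show that modest shortfalls are not reliably caught.

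**Step 3. The two benchmarks on means.** The article gives no standard deviations, so these are assumptions, shown as ranges. The half-width of a 95% interval is t(0.975, n−1) × SD/√n, with t = 2.093 for n=20.

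- Lesson completion, assumed SD 25–40 points: from 2.093 × 25/√20 = 11.7 to 2.093 × 40/√20 = 18.7 points around 60%.
- Acceptability ratings, assumed SD 0.7–1.2: from 2.093 × 0.7/√20 = 0.33 to 2.093 × 1.2/√20 = 0.56. A mean of 3.6 is 0.1 from the 3.5 cut-off and cannot be told from it anywhere in that range.

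**The case against.** Several points on the other side are good ones.

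**The cut-offs do discriminate.** A reader might infer from the intervals that 20 to 40 people cannot separate adequate from clearly inadequate feasibility. That goes too far. If clearly inadequate means 20 points below a benchmark, the rule passes it under 1% of the time at n=40 and about 4% of the time for 17/20. The article does not define inadequate, so no stronger statement is available.

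**The pass rate at the benchmark itself is not evidence.** A true rate exactly at the cut-off passes only 57–59% of the time at n=40 and 65% for 17/20. It is tempting to read this as a sign that N is too small. It is a property of any point-estimate cut-off: for these four rates it is 52–53% at n=400 and about 51% at n=4000.

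**Ratings can be told from neutral.** A reader might also suppose that a mean of 3.6 could not be distinguished from the scale midpoint of 3. At n=20 the half-width stays below 0.6 throughout the assumed SD range, so it can. With 15 raters it fails only if the SD exceeds about 1.08.

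**The 17/20 case may rarely arise.** Intervention participants complete session 1 within the baseline visit, so the at-least-one-module benchmark is close to automatic. The n=20 figures are best read as showing the precision of any rate in that arm.

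**This is a condensed article on a pilot.** Small N is normal, the article admits it, no formal go/no-go rule is stated, and an unseen analysis plan may already call for intervals. All of that stands, so the absence of intervals alone would not be a finding. What remains is the published claim of sufficiency, which is made here without support, and the denominator, on which two sections of the article disagree.

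**Conclusion.** The point holds in a limited form. The sufficiency statement is unsupported: N rests on practical grounds, and the described analysis compares point estimates with fixed cut-offs. N=40 is enough to identify gross infeasibility. It is not enough to detect shortfalls of 5–10 points reliably: such rates pass 11–32% of the time for the n=40 benchmarks and 23–41% for 17/20. The documents do not support the stronger reading that the design cannot recognise clearly inadequate feasibility.

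The proportion results use only the article's own rates and sample sizes, under a binomial model with every randomized participant counted; 17/20 applies the analysis section's denominator to the 85% benchmark. The results for means depend on assumed standard deviations. The printed 34/40 is inconsistent with the intervention-arm rule whatever view is taken of precision.

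**What to change.** 1. In Statistical Analysis, Feasibility and Acceptability, state that each benchmark will be reported with a two-sided 95% confidence interval: exact or Wilson for proportions, t or bootstrap for lesson completion and rating means. Use the intervention arm for module completion, lesson completion and acceptability.
2. In Feasibility Benchmarks, restate 34/40 as 17/20 so that it agrees with the analysis section.
3. In Strengths and Limitations, replace the sufficiency sentence with the precision available. For example: N=40 can identify gross infeasibility, but a just-met visit-completion benchmark has a 95% interval reaching about 16–17 points below and 11–14 points above the estimate, and intervention-arm rates are less precise.

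The cost is a few sentences and some intervals in the results table. No extra participants are needed, and the article expects analysis by May 2027, so this can be settled beforehand. The downside is a less favourable account of what the pilot can show.

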### Future Directions

Nevertheless, the study has the potential to be an important step in developing a digital treatment that will provide large-scale delivery of a treatment for BED. This project can serve as a foundation for a full-scale efficacy RCT. A digital treatment can offer unprecedented possibilities for dissemination in the real world. Finally, although this study focuses on BED, results from this study could inform the development of a similar intervention for other EDs.

## Appendix

Multimedia Appendix 1 Summary of the 16 core lessons in Cognitive behavioral therapy–based Mindful Courage.

Multimedia Appendix 2 Summary of study measures.

Multimedia Appendix 3 Peer review report from ZAT1 JM (13) - National Center for Complementary and Integrative Health Special Emphasis Panel, NCCIH Training and Education Review Panel (National Institutes of Health, USA).

## Abbreviations

BED: binge eating disorder
CBT: cognitive behavioral therapy
ED: eating disorder
EDE-Q: Eating Disorder Examination Questionnaire
HIPAA: Health Insurance Portability and Accountability Act
MBI: mindfulness-based intervention
NCCIH: National Center for Complementary and Integrative Health
RCT: randomized controlled trial
